### Interventions

2.8

#### Experimental intervention

2.8.1

At emergency room admission, the antiplatelet medication will be discontinued and platelet function will be determined. In patients with >80,000 functional platelets, the surgery will be scheduled within the next 24 hours. However, if the level of functional platelets is <80,000, then the platelet assay will be performed once per day for the next 2 days or until normalized (whichever occurs first): surgery will be performed within 24 hours after normalization. If the number of functional platelets has not normalized after 3 days, surgery with neuraxial anesthesia will be scheduled in accordance to the margin of safety time established for the specific antiplatelet medication.

#### Control intervention

2.8.2

Antiplatelet therapy will be discontinued at admission to the emergency room. Surgery with neuraxial anesthesia will be performed in accordance with the established safety time for the antiplatelet drug. Platelet function will be determined the day before surgery but the results will not be revealed to the researchers until the end of the study.

#### Co-intervention

2.8.3

All included patients must be eligible for neuraxial anesthesia.

#### Description of the surgical intervention

2.8.4

The specific surgical technique—osteosynthesis, hemiarthroplasty, or total hip arthroplasty—will depend on the characteristics of the proximal femur fracture in each patient. Osteosynthesis will be performed with cannulated screws, Dynamic Hip Screw with plate (DHS), or intramedullary nail (short or long), depending on the fracture type. Displaced subcapital fractures will be treated by hemiarthroplasty (monopolar or bipolar) or total hip arthroplasty, depending on the patient characteristics. Total arthroplasty can be cemented, uncemented, or hybrid. In all cases, the orthopedic surgeon will follow the surgical protocol in place at the treating hospital for the type of fracture. Each center will follow the specific transfusion protocol in place at that institution.

### Statistics

2.9

#### Sample size estimation

2.9.1

One of the participating centers used historical data from the hospital database to calculate the mean time from admission to surgical intervention in patients not receiving antiplatelet treatment and without any coagulopathies: 2.85 days (standard deviation [SD], 3.17). Accepting an alpha risk of 0.05 and a beta risk under 0.20 in a 2-sided contrast and a 10% loss rate, the estimated sample size needed to detect a decrease of ≥1.5 days from admission to surgery was 156 patients (78 subjects in the experimental and control groups, respectively). This calculation was made using v. 7.10 (June 2010) of the GRANMO calculator (available at: https://www.imim.es/ofertadeserveis/en_granmo.html).

#### Data analysis

2.9.2

The main analysis of efficacy will be made “per protocol”, but an analysis on an Intention-To Treat (ITT) basis will be done to test the consistency of the results. In the “per protocol” analysis will be included patients that have received the corresponding test for platelet function and have been undergoing surgery. In the ITT, analysis will be included all patients randomized independently if they have received the test or the surgery.

The 2 groups will be compared to ensure that there are no significant differences in the clinical variables of interest. Student's *t* test will be applied to check for between-group differences in the main study endpoint (mean time from admission to surgery). The specific statistical analysis of the baseline characteristics will depend on the nature of the evaluated variables. For categorical variables, we will use the chi-square test with the corresponding contingency table. Ordinal or quantitative variables with clear non-normal distribution will be analyzed using the nonparametric test for more than 2 groups (Kruskall-Wallis), including medians with ranges for each group. The *t* test will be used to assess quantitative variables that meet normality criteria, with mean values and SD provided for each group.

All variables showing statistically significant or clinically relevant differences between the groups on the initial comparison will be entered into a multivariate model to confirm that the differences relative to the study's main endpoint remain significant on an analysis of covariance.

The EQ-5D-5L measures 5 dimensions (mobility, self-care, usual activities, pain/discomfort, and anxiety/depression) related to quality of life. Each dimension has 5 levels of severity (no problems, slight problems, moderate problems, severe problems, and extreme problems) which are scored from 1 (no problems) to 5 (extreme problems) points, with the maximum score of 1 indicating a state of full health. The partial results on each dimension and the overall score will be calculated using the scoring algorithms developed by Ramos-Goñi et al.^[24]^ Because this questionnaire yields ordinal data, nonparametric tests will be used to analyze the comparisons. Between-group differences will be analyzed using the Mann-Whitney and Kruskal-Wallis tests.

The EQ-VAS evaluates patient-perceived health status. This is a vertical scale ranging from 0 to 100. An ANalysis Of VAriance (ANOVA) will be performed.

For the economic analysis, we will calculate the costs in Euros (€) based on the prices of the local health system. For the cost-effectiveness analysis, the costs of the study intervention will be compared to the incremental results, measured in natural units. Cost-effectiveness will be measured by the time from hospital admission to first mobilization after surgery. If the results in the 2 groups are similar, we will perform a cost minimization analysis. Data will be converted into a unit-cost evaluation to determine average cost per patient. We will conduct a comparative economic evaluation of the 2 study alternatives. Confidence intervals will be used to determine the presence of significant differences.

To perform the cost-utility analysis, we will assess Quality-Adjusted Life Years (QALYs)—measured with the EQ-5D-5L—and cost per QALY, calculated incrementally (Δ cost/Δ QALYs) in each group.

We will perform a deterministic sensitivity analysis to evaluate the robustness of the results. The level of significance for all statistical analyses will be set at 5%. The SPSS statistical software program (v. 24) will be used to perform the statistical analyses.

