### Study design

2.1

Multicenter, randomized, open-label, parallel clinical trial of patients receiving chronic antiplatelet therapy admitted to the emergency department with a femoral fracture. All study participants will undergo platelet function testing and those with more than 80,000 functional platelets will be randomized to either early surgery with neuraxial anesthesia or delayed surgery with neuraxial anesthesia performed in accordance with the antiplatelet activity time of the specific antiplatelet drug (3 days for aspirin 300 mg/day and triflusal 600 mg/day; 5 days for clopidogrel and ticagrelor; 7 days for prasugrel, and 10 days for ticlopidine).

Recruitment started in September 2017 and will continue until December 2019. The last follow-up visit for the final patient included in the study will be in December 2020. To date, 81 patients have been included.

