#### Criteria for withdrawal from the clinical trial

2.3.4

The emergence of any of the following events may justify study withdrawal: severe adverse event, any clinical condition preventing the patient from continuing in the trial, protocol violations, the patient's voluntary decision to withdraw, loss to follow-up, or death.

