### Blinding

2.6

Necessarily, the patients and researchers will know which intervention they have been allocated. However, to avoid influencing the timing of the surgical procedure, the investigators will be blinded to the platelet function status in the control group.

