### Implementation and data collection

2.7

Figure 1 describes the patient recruitment process and the study plan. A competitive recruitment process will be used; thus, no predetermined limit to the total number of patients per center has been established. Patient selection will be performed on the day of admission to the hospital emergency department. Researchers will first verify that the patient meets the study inclusion criteria. The patient will then be informed about the clinical trial and asked to participate. Patients who agree to participate will be enrolled in the study after signing the informed consent form. Next, they will be randomized to one of the 2 study groups.

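### The main efficacy analysis is per protocol, on a set defined by events after randomisation, so the primary comparison is open to bias of unknown size and direction

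*Protocol article*

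**What the plan says.** Section 2.9.2 of the protocol article sets the order of the two analyses: "The main analysis of efficacy will be made “per protocol”, but an analysis on an Intention-To Treat (ITT) basis will be done", and gives the second the role of testing whether the results are consistent. The per-protocol set consists of "patients that have received the corresponding test for platelet function and have been undergoing surgery". The ITT set is the wider one: "analysis will be included all patients randomized independently if they have received the test or the surgery".

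The design is "Multicenter, randomized, open-label, parallel clinical trial of patients receiving chronic antiplatelet therapy", and section 2.6 adds: "Necessarily, the patients and researchers will know which intervention they have been allocated". The endpoint is the time from emergency room admission to surgery (2.4.1), compared by Student's t test. The sample size (2.9.1) rests on a two-sided test for a decrease of at least 1.5 days. No margin is given.

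Section 2.3.4 lists reasons for leaving the study: "The emergence of any of the following events may justify study withdrawal: severe adverse event", followed by, among others, protocol violations and death.

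**The concern.** Randomisation protects a comparison only if patients are analysed in the groups to which they were allocated. Here, membership of the main analysis set depends on two later events: having the test that belongs to the arm, and having surgery. The two arms reach these events by different routes. An experimental patient is tested at admission. A control patient is tested only on the day before surgery, after a drug-specific wait of 3 to 10 days. During that wait a control patient may die, become unfit, withdraw or be operated on without the test.

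Exclusion can thus depend on the arm and on the course of the wait, and the wait is the endpoint. Staff know the allocation, so departures from the schedule may also depend on it. The usual reason for giving weight to a per-protocol analysis, a non-inferiority claim, does not apply, because the hypothesis is one of difference. The article gives no other reason for the choice. What is at stake is which patients produce the trial's primary answer.

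**Working it through.** **The plan's own figure.** Inputs from 2.9.1: SD 3.17 days, difference 1.5 days, two-sided alpha 0.05, power 0.80, loss 10%.

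n per arm = 2 × [SD × (z0.975 + z0.80) / difference]² = 2 × [3.17 × (1.960 + 0.842) / 1.5]² = 70.11. Then 70.11 / (1 - 0.10) = 77.9, rounded up to 78 per arm, or 156 in total. The stated figure reproduces. (Rounding up to 71 before allowing for loss would give 79 per arm, or 158.)

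**When the two conditions are met.**

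- Randomisation: section 2.7 places it directly after consent on the day of admission: "Next, they will be randomized to one of the 2 study groups". Section 2.1 instead describes a platelet test in all participants, with only those above 80,000 functional platelets then randomised.
- Experimental test: at admission (2.8.1). The same section describes patients below 80,000 who are already in the experimental arm, which does not fit 2.1.
- Control test: the day before surgery (2.8.2), so after randomisation on either reading.
- Surgery: after randomisation in both arms on either reading.

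**Whom the definition removes.** It removes patients without the required test and patients without surgery. It does not require surgery at the allocated time. Among patients who have a time to surgery, per protocol and ITT therefore differ only in those operated on without the required test. Let f be their share of the operated controls, R the mean wait of those retained and E the mean wait of those excluded. The mean of all operated controls is (1 - f)R + fE, so

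per-protocol control mean - mean of all operated controls = f × (R - E).

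The article gives neither f nor R - E. If one assumes R - E = 3 days (for example 4 against 1) and f = 0.05, 0.10 or 0.15, the gap is +0.15, +0.30 or +0.45 days, which is 10%, 20% or 30% of 1.5 days. If R - E = -3 days, the same figures apply with a minus sign. If these patients were in fact tested, they stay in the set and the gap is zero.

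**Worst-case bounds by simulation.** Assumptions not in the article: 78 per arm; SD 3.17 in both arms; control mean 2.85 days (the historical mean in 2.9.1, which comes from patients without antiplatelet treatment); exclusions in controls only; those removed always have the longest or always the shortest waits. There were 20,000 runs per scenario. Ranges cover gamma and normal waiting times. The difference is control minus experimental, in days.

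| Controls removed | Estimate, true difference 0 | Two-sided error | Estimate, true difference 1.5 | Power |
|---|---|---|---|---|
| none | about 0 | about 0.05 | 1.50 | about 0.83 |
| 4, longest | -0.50 to -0.33 | 0.11 to 0.21 | 1.00 to 1.16 | 0.60 to 0.65 |
| 4, shortest | 0.15 to 0.35 | 0.06 to 0.12 | 1.65 to 1.84 | 0.88 to 0.96 |
| 8, longest | -0.82 to -0.62 | 0.25 to 0.48 | 0.69 to 0.88 | 0.39 to 0.44 |
| 8, shortest | 0.32 to 0.62 | 0.10 to 0.25 | 1.82 to 2.12 | 0.92 to 0.99 |

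Eight of 78 is 10.3%, about the loss already planned for.

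**Power for all randomised patients.** By the normal approximation for a comparison of means, power is 0.840 with 78 per arm and 0.799 with 70 per arm, which is the planned level.

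**The case against.** The strongest reply is that this per-protocol set is mild. A control operated on early but tested the day before stays in. Section 2.1 says that all participants are tested, so few operated patients may be lost. Losses need not fall on controls alone: experimental patients below 80,000 functional platelets also wait, possibly for the full safety time of their drug, and may die or become unfit meanwhile. ITT is planned and would expose a discrepancy. Besides, a patient never operated on has no time to surgery, so a t test drops that patient under either label.

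Most of this stands, and it limits what can be claimed. Three stronger readings are tempting, and the article supports none of them.

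- A reader might infer that the primary result is biased, and biased towards the experimental arm. The number of exclusions and the reasons for them are unknown, and the bounds run in both directions.
- A reader might infer that controls operated on early are dropped as such. Only those who also lack the test are dropped.
- A reader might infer from section 2.3.4 that adverse events are deleted from the secondary outcomes. The section is permissive and does not say that recorded data are removed. Serious events have their own notification route (2.10), and complications are taken from medical records (2.7). What is at risk is follow-up after withdrawal.

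The reply does not justify the order of the two analyses. A mild set is still formed after randomisation, under different conditions in each arm, and a consistency check does not say which result prevails if the two disagree. The word superiority is not used in the article, but a two-sided test for a difference without a margin amounts to it.

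**Conclusion.** The point holds as a matter of design. The main analysis rests on a set selected after randomisation in an open-label trial of difference, and the article neither justifies nor offsets this. The conflict over whether a test precedes randomisation does not remove it, since the control arm's test and all surgery come later on either reading.

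The comparison is open to bias, with size and direction unknown. The shift of -0.82 to +0.62 days for 8 excluded controls is an extreme bound under the stated assumptions, not a forecast. It does show that exclusions no larger than the planned loss could change the conclusion. Exchanging the two labels alone would be incomplete, because patients without surgery would still drop out of the t test.

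**What to change.** - In 2.9.2, make the analysis of all randomised patients, as allocated, the main efficacy analysis, and per protocol supportive.
- State how patients never operated on, including deaths before surgery, enter the primary analysis. Options are time to surgery with death as a competing event, or a rank-based analysis that gives these patients a worst value.
- In 2.3.4, state that patients withdrawn for an adverse event or a protocol violation stay in follow-up and in the analysis unless they withdraw consent, and that death counts as an outcome. This concerns data retention only.
- Reconcile sections 2.1, 2.7, 2.8.1 and 2.8.2 on when the platelet test is done relative to randomisation.

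The cost is wording and a little analysis work. Dates and times of admission and surgery are already among the planned data (2.7), both analyses are already foreseen, and the sample size stays at 156. The power figures above apply to a comparison of means; a competing-event or rank-based analysis would need its own short check. The estimated effect may be somewhat smaller. The article reports 81 of 156 patients included, so at that stage the order could still be set before results were known.

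### The main efficacy analysis is per protocol, in a set defined by post-randomisation events that differ by arm, while ITT serves only as a consistency check

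*Protocol article*

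**What the plan says.** All references are to the protocol article.

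- **Main analysis (2.9.2).** "The main analysis of efficacy will be made “per protocol". Of ITT the section says that "an analysis on an Intention-To Treat (ITT) basis will be done to test the consistency of the results".
- **Per-protocol set (2.9.2).** In this "analysis will be included patients that have received the corresponding test for platelet function and have been undergoing surgery".
- **ITT set (2.9.2).** In this "analysis will be included all patients randomized independently if they have received the test or the surgery".
- **Test in the experimental arm (2.8.1).** "At emergency room admission, the antiplatelet medication will be discontinued and platelet function will be determined". It is repeated daily if the result is below the threshold.
- **Test in the control arm (2.8.2).** "Platelet function will be determined the day before surgery but the results will not be revealed". Surgery follows a drug-specific wait, which section 2.1 puts at 3 to 10 days.
- **Aim (2.9.1).** The calculation gives "the estimated sample size needed to detect a decrease of ≥1.5 days from admission to surgery", with a two-sided test. No non-inferiority margin appears, and no reason is given for putting per protocol first.
- **Blinding (2.6).** Patients and researchers know the allocation. Only the platelet results of the control arm are concealed.

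**The concern.** The article never uses the word superiority, but the aim of detecting a decrease, with no margin, makes this a superiority comparison. In such a trial the main result should rest on the groups that randomisation created. Here it rests on a subset chosen by what happened afterwards.

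Two features make this set more exposed than an ordinary per-protocol set. First, the qualifying test comes at different times in the two arms. An experimental patient can have it on arrival. A control must stay in the trial through the wait, and have surgery scheduled predictably enough for a sample the day before. Second, the timing of the control test is tied to the timing of surgery, which is the primary outcome. A control whose surgery is brought forward may lack the sample and would also have a short time to surgery. Deaths, withdrawals and protocol violations (2.3.4) also have longer to occur before surgery in the control arm.

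At stake is which result counts as the trial's conclusion. As written, a favourable per-protocol result would stand as the main finding even if ITT were weaker.

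**Working it through.** **1. The plan's own figure.** Inputs from 2.9.1: difference 1.5 days, SD 3.17, two-sided alpha 0.05, power 0.80, loss 10%.

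n per arm = 2 × [3.17 × (1.960 + 0.842) / 1.5]² = 70.1. Dividing by 0.9 gives 77.9, so 78 per arm and 156 in total. The stated size reproduces. The issue is bias, not sample size. Power by the normal approximation is 0.84 with 78 per arm analysed and 0.80 with about 70 per arm.

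**2. Which conditions come after randomisation.**

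| Condition for the per-protocol set | Experimental arm | Control arm |
|---|---|---|
| Platelet test | At admission (2.8.1) | Day before surgery (2.8.2) |
| Surgery | After randomisation | After randomisation |

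Sections 2.1 and 2.7 disagree on the order of events. Section 2.1 has everyone tested and only those above the threshold randomised; section 2.7 has randomisation directly after consent. If 2.1 is right, the experimental arm's admission test may precede randomisation. The control arm's day-before test and surgery in both arms still follow it, so the difference between the arms remains if the corresponding test in the control arm is the one described in 2.8.2.

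**3. Size, by formula.** The documents give no exclusion rates, so everything from here is assumption. Suppose there is no true effect and a share f of controls is excluded, whose mean time is g days below the mean of their arm. The control mean then rises by f × g / (1 − f). With 78 per arm and SD 3.17, SE = 3.17 × √(1/78 + 1/[78(1 − f)]). The two-sided type I error is 1 − Φ(1.96 − shift/SE) + Φ(−1.96 − shift/SE).

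| f | g (days) | Shift (days) | Type I error |
|---|---|---|---|
| 2% | 3.17 | 0.02 × 3.17 / 0.98 = 0.065 | 0.052 |
| 5% | 3.17 | 0.05 × 3.17 / 0.95 = 0.167 | 0.062 |
| 10% | 3.17 | 0.10 × 3.17 / 0.90 = 0.352 | 0.104 |
| 15% | 3.17 | 0.15 × 3.17 / 0.85 = 0.559 | 0.184 |
| 10% | 1 | 0.10 × 1 / 0.90 = 0.111 | 0.055 |

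If the excluded controls waited longer than average, the sign of the shift reverses.

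**4. Size, by simulation.** Both arms have the same positive, skewed distribution (lognormal or gamma) with an assumed mean of 4 days and SD 3.17. There are 78 per arm, the earliest-operated controls are deleted, and Student's t test is applied. This is a worst case, because every deleted control is the most extreme available.

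| Controls lost | Bias (days) | Type I error |
|---|---|---|
| 4 of 78 (5%) | 0.17 to 0.20 | about 7 to 8% (6.6% in the lowest run) |
| 8 of 78 (10%) | 0.34 to 0.39 | about 11 to 13% |

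Against the 1.5-day target, 0.34 to 0.39 days is 0.34/1.5 = 23% to 0.39/1.5 = 26%. If the lost controls come at random from the shortest third instead, the type I error is about 6% at 5% lost and 8 to 10% at 10% lost.

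**The case against.** **Direction.** A reader might infer that the per-protocol result must favour the experimental arm. The documents do not show this. Section 2.9.2 excludes for a missing test, not for surgery outside the planned window, so a control operated on early but sampled the day before stays in. A control whose surgery date slipped, and who missed the sample for that reason, drops out, and that narrows the difference. So does losing a quickly operated experimental patient whose test was missed. This part of the objection stands: direction is plausible in one scenario, not established.

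**Size.** The same worst case with normally distributed times gives type I errors of about 12% and 25%. Those figures should not be used. With mean 4 and SD 3.17, 10.4% of normal times are negative, and the 5% and 10% cut-offs lie at −1.21 and −0.06 days, so the deleted controls would mostly have had surgery before admission.

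**The set is close to a modified ITT.** Surgery is needed for the endpoint (2.4.1) to exist, so only the missing-test condition removes patients with an observed outcome. The only loss figure is 10% (2.9.1), for both arms and any cause. This limits the likely size, but a condition tied to surgical timing is still being used to choose the main set.

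**Mitigation.** ITT is pre-specified, so a discrepancy would be visible, and control results are concealed to protect the timing of surgery. Neither changes which analysis carries the conclusion.

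**ITT is not complete as written.** A reader might infer that swapping the labels yields an unbiased analysis. It does not by itself: randomised patients never operated on have no time to surgery, and the named t test cannot include them.

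**Conclusion.** The point holds as a matter of analysis set. The per-protocol choice is stated outright, so it is not something left to a fuller document. It makes the main result depend on post-randomisation events that differ by arm and can be linked to the outcome, in an open-label trial.

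The bias is small if few patients are excluded and material if exclusions come near 10% of one arm. In the assumed worst case it is about 0.17 to 0.20 days at 5% of controls lost and 0.34 to 0.39 days at 10%; less extreme exclusion gives less. These figures rest on no true effect, 78 per arm, mean 4 and SD 3.17 days, positive skewed times, and loss of the earliest-operated controls only. The actual exclusion rate, and so the actual size, cannot be derived from the article. Uncertainty about the direction is a further reason not to rest the conclusion on this set.

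**What to change.** In 2.9.2:

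1. Make ITT the main analysis: all randomised patients, in the arm assigned, whether or not tested. State that the trial's conclusion follows it.
2. Make per protocol supportive, and do not use receipt of the platelet test as a condition for the main set.
3. State how randomised patients who never have surgery are handled, for example by a time-to-event analysis from admission with death before surgery as a competing event.

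Also reconcile 2.1 with 2.7 and 2.8.1 on whether a platelet test precedes randomisation, and say which test counts as the corresponding one in each arm.

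**Cost.** The sample size stays at 156. Dates and times of admission and surgery are already key variables (2.7). The article reports 81 patients included at the time of writing, so the change could precede the final analysis. The downsides are a possibly smaller estimated effect and somewhat more analysis work for patients without surgery.

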#### Main outcome

2.4.1

Time, in hours, from emergency room admission until surgery.

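### The ITT analysis of time to surgery includes patients who are never operated on, but the only test named for that endpoint has no value for them

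*Protocol article*

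**What the plan says.** The main outcome (section 2.4.1) is "Time, in hours, from emergency room admission until surgery". Section 2.9.2 names one test for it, without conditions: a Student's t "test will be applied to check for between-group differences in the main study endpoint (mean time from admission to surgery").

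The same section fixes two analysis sets:

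- **Per protocol**, the main efficacy analysis: "patients that have received the corresponding test for platelet function and have been undergoing surgery".
- **ITT**, in second place: "but an analysis on an Intention-To Treat (ITT) basis will be done to test the consistency of the results". Its members are "all patients randomized independently if they have received the test or the surgery".

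Section 2.3.4 lists reasons for leaving the trial. They include death, a clinical condition that prevents continuing, voluntary withdrawal and loss to follow-up. Sections 2.1 and 2.8.2 set the control arm's wait by drug, from 3 to 10 days. Section 2.8.1 schedules surgery within 24 hours for experimental patients with enough functional platelets.

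The only distribution figures for the endpoint are in section 2.9.1: a historical mean of "2.85 days (standard deviation [SD], 3.17") from one centre's patients who were not on antiplatelet treatment.

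**The concern.** The endpoint, the test and the ITT set are each fixed in the article, and they do not fit together. A t test on mean time needs a time for every patient. The ITT set expressly takes in patients who have none.

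At stake is the only check on the main analysis. The per-protocol set is selected after randomisation, on having been tested and operated on. The ITT analysis is there to show whether that selection changes the answer. If it loses the same unoperated patients, agreement between the two results says almost nothing about the selection.

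The selection may also be related to allocation. Controls spend longer exposed to death, deterioration or withdrawal before surgery, and the Discussion itself links delay beyond 48 hours to higher morbidity and mortality.

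**Working it through.** **1. The plan's own sample size, for reference.** Inputs from section 2.9.1: SD 3.17 days, difference 1.5 days, two-sided alpha 0.05, power 0.80, 10% loss.

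n per arm = 2 × [SD × (z0.975 + z0.80) / difference]² = 2 × [3.17 × (1.960 + 0.842) / 1.5]² = 70.1.

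70.1 / 0.90 = 77.9, so 78 per arm and 156 in total. The stated figure reproduces. It rests on a comparison of means in about 70 evaluable patients per arm.

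**2. What the ITT analysis becomes.** Split the randomised patients into three groups:

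| Group | Has a time to surgery? | In per-protocol set? | In ITT set as defined? | In ITT t test as run? |
|---|---|---|---|---|
| A. Tested and operated | yes | yes | yes | yes |
| B. Operated, not tested | yes | no | yes | yes |
| C. Never operated | no | no | yes | **no** |

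The defined ITT set is A + B + C, but the t test can use only A + B. It differs from the per-protocol analysis by group B alone. Group C is in no analysis of the main endpoint.

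**3. How large group C could be.** The documents give no share. As an assumption, take 0 to 10%: 0 to 0.10 × 156 = 15.6 patients, or 0 to 7.8 per arm if equal. The 10% loss rate in section 2.9.1 is an allowance for losses of any kind and is not an estimate of group C. The direction and size of any bias cannot be computed from the documents.

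**4. Does skew undermine the t test?** SD/mean = 3.17 / 2.85 = 1.11. A normal distribution with these values would put Φ(−2.85/3.17) = Φ(−0.90) = 18% of times below zero, so the historical times must be right-skewed. Simulation with 70 per arm and 5,000 trials per setting, using lognormal and gamma times:

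| Setting | t test | Mann-Whitney |
|---|---|---|
| No difference, SD 3.17 (type I error) | 0.049–0.052 | 0.048–0.053 |
| 1.5-day difference, SD 3.17 in both arms | 0.79–0.83 | 0.97–1.00 |
| Constant SD/mean, lognormal, 2.85 v 1.35 | 0.97 | 1.00 |
| Constant SD/mean, lognormal, 4.35 v 2.85 | 0.64 | 0.78 |
| Constant SD/mean, gamma, 2.85 v 1.35 | 0.97 | 0.90 |
| Constant SD/mean, gamma, 4.35 v 2.85 | 0.59 | 0.47 |

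The t test keeps its type I error and, at the plan's SD, its designed power. Which test has more power depends on the assumed shape. In the 4.35 v 2.85 rows the t test falls short of 80% because a constant ratio raises the slower arm's SD to 4.35 × 1.11 = 4.84, above the plan's 3.17.

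**5. What including group C does to power.** With 78 per arm, 10% never operated in each arm and SD 3.17 in both arms:

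- t test on operated patients only: 0.78–0.85
- rank test with unoperated patients ranked last: 0.89–1.00
- log-rank with unoperated patients censored late: 0.49–0.90

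These are unstratified stand-ins; Gray's test and the van Elteren test were not simulated.

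**The case against.** - **The main analysis is unaffected.** This stands. The per-protocol set contains only operated patients, so its t test can be computed. Unoperated patients are absent from it because of the set definition, and another test on the same set would leave out the same people. The point concerns the ITT analysis only.
- **Handling of unoperated patients belongs in an analysis plan that is not shown.** This would answer a mere gap. Here the article itself fixes both the ITT membership and the test, and the two cannot both be followed.
- **Differential loss is not shown.** This stands. It is plausible from the drug-specific waits and the listed reasons for leaving, but there is no rate of death or cancellation before surgery.
- **Skew.** A reader might infer from an SD above the mean that the t test is invalid or that power is lost. The documents do not support this. Type I error and planned power hold at the plan's own SD, and a rank test gains under some shapes and loses under others. The figures also come from patients not on antiplatelets, whereas trial times are shaped by fixed waits and a 24-hour target, so skew in the trial arms is inferred.
- **Contradiction with the plan's rank-test rule.** A reader might also see one in "Ordinal or quantitative variables with clear non-normal distribution will be analyzed using the nonparametric test". That sentence follows the one on baseline characteristics and is not tied to the main endpoint.

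**Conclusion.** The point holds for the ITT analysis. As written it cannot be carried out on the set the article defines. In practice it falls back to operated patients, which is nearly the per-protocol set, so it does not test consistency against the selection that matters. No planned analysis of time to surgery retains all randomised patients.

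The size depends on how many are never operated on and how evenly they fall between the arms. The documents give neither. The range of 0 to about 16 of 156 is an assumption.

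The point does not extend to the validity of the main t test or to the planned power. The historical skew supports a rank-based sensitivity analysis and no more.

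**What to change.** State how randomised patients without surgery enter the ITT comparison, and use one of these on all randomised patients:

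1. Cumulative incidence of surgery from admission, with death or a decision not to operate as a competing event and withdrawal or loss before surgery censored, compared by a centre-stratified Gray's test.
2. A centre-stratified worst-rank (van Elteren) test that gives patients known not to have been operated on the longest time. It needs a stated rule for patients withdrawn or lost before surgery, who may have been operated on outside the trial.

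Report the difference in median or restricted-mean hours, so that the result stays on the time scale of the 1.5-day target. Keep the t test on operated patients, add a rank-based sensitivity analysis, and report the number never operated on, by arm and reason.

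**Cost.** The change is to analysis wording. The date of death or of the decision not to operate must be taken from the medical record, which section 2.7 already uses as a source, although its list of key variables does not include the decision date. The ITT result is no longer a simple mean difference. Its power may be higher or lower than that of the t test on operated patients, so the change should be justified by completeness and not by a gain in power.
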